## Study objectives

The main objective of this study is to investigate the effect of the Paula exercise method on urine leakage among women who suffered post-fistula repair incontinence (PFRI). In addition, the study will investigate the following:Effect of the Paula exercise method on pelvic floor strength in women who suffered PFRI.Effect of the Paula exercise method on quality of life of women who suffered PFRI.Effect of the Paula exercise method on sexual function in women who suffered PFRI.Effect of the Paula exercise method on mental health in women who suffered PFRI.

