## Methods

### Study design and sample

The research design for this study is a randomized controlled trial (RCT). It is a quantitative research in the form of pretest, posttest and follow-up design. The study will be a two-arm, outcome assessor-blinded RCT. The two-arms will comprise an intervention and a control. Following participants’ consent and baseline assessments, eligible participants shall be allocated randomly into either the intervention group (Paula exercise method) or the control group (pelvic floor muscle training). The proposed timeline for this study is 12 calendar months from participants’ enrolment to follow-up assessments; Table 1 below:

**Table 1 Tab1:** Study timeline from enrolment to completion

	Enrollment	Allocation	Post-allocation				Follow-up
Time point	− t	0	t0 (0 week)	t1 (4 weeks)	t2 (8 weeks)	t3 (12 weeks)	t4 (6 months)
Enrollment: eligibility screen informed consent allocation	X						
	X						
		X					
Intervention: Paula exercise (experimental group) Pelvic floor muscle training (control group)			X	X	X	X	
			X	X	X	X	
Assessments: baseline variables—age, weight, height, blood pressure, marital status, educational status, post fistula repair time	X	X					
Assessments: outcome variables [Primary outcome- urine leakage] [Secondary Outcome- pelvic floor strength, quality of life, sexual function, depression and anxiety]			X	X	X	X	X

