### Participants

Participants in this study will comprise all women with PFRI attending the obstetrics and gynaecology departments of MMSH and JGH. However, only women who meet the study inclusion criteria will be screened and randomized into the experimental (Paula Exercise Method) and control (Pelvic Floor Muscles Training) groups. Participants will be screened for eligibility by the researcher and the research assistants. Participants will be considered eligible if: they have had the PFRI for more than 3 months, to ensure that healing has taken place [1, 14]; they present with a 1 g gain in weight following a pad test; they consent to participate through a written informed consent; they are not above the age of 50 because as women age changes occur in the bladder and pelvic structures that can increase the risk of developing incontinence [36]; they have no faecal leakage; they have not had previous rectal surgery; they are not receiving any other alternative PFM rehabilitation at the point of recruitment; and urinary infection is ruled out because it affects the integrity of the pelvic organs [37].

After screening for eligibility, a cough test will be used to differentiate the type of incontinence. In the cough test, if urine leakage coincides with the cough, it is classified as stress incontinence (SI), however, if the leakage is delayed till after the cough, it is urge incontinence. No leakage after the cough signifies that it is overflow and functional incontinence [38].

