### Sample size

The sample size of this study was estimated based on the findings of a pilot study. We conducted a pilot study to test the adequacy and feasibility of this protocol as well as to determine the sample size required for this study. The pilot study participants were recruited after being certified as eligible to participate using the specified study inclusion criteria. Recruitment was conducted by reviewing records of the outpatient urology clinic on a weekly basis. A total of 30 women with post fistula repair incontinence participated in this pilot study. The 30 subjects were randomly assigned into the two arms of the study resulting into 15 participants in each arm of the pilot study (Paula Exercise Method and Pelvic Floor Muscle Training groups). All participants were assessed at baseline before randomization and prior to the commencement of intervention, post intervention (outcome). The primary outcome of interest is Urine leakage. The programme was structured for 4-weeks of daily routine activities in both groups. The detail of urine leakage assessment is described later in the manuscript as the primary outcome measure.

In this pilot study the mean age of participants was 29.9 ± 9.4, the median Urine leakage score for PEM and PFMT was 4.53 g and 21.61 g respectively. We computed Mann Whitney U for the data because the data was not normally distributed. Result for an independent two groups non-parametric test indicated significance (*U* = 38.00,* p* = 0.020) with an effect size of *Ƞ*^2^ = 0.32.

Using the outcome of the pilot study and according to a power calculation to detect a between-group difference, of 0.3 effect size for two independent means Mann Whitney U in urine leakage (UL) with 90% power at α = 0.05, a total sample size of 166 was generated. This suggests a total of 83 participants in each group. A 10% attrition rate will be considered, therefore, 182 participants will be recruited giving 91 participants in each group. The recruitment of participants from the two hospitals would be accomplished by: involving the surgeons from the departments of obstetrics and gynaecology of both hospitals who are involved in performing the fistula repairs (in the recruitment); and reviewing hospital registry and subsequently contacting patients whose records are available through individual phone contacts.

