### Randomization

After screening the participants, and following baseline assessments, a computer-generated random allocation sequence will be used to assign the participants to either the intervention group (PEM group where they will receive PEM plus PFMT), or the control group (where they will receive PFMT only). To eliminate bias, the randomization will be carried out by a third party who is not aware of the study group. Assessment of outcome will be carried out by an experienced/trained researcher, who will be blinded to the type of intervention received by participants in each group. The study participants’ flow diagram is presented in Fig. 1

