### Interventions

The interventions for the study will be PEM and PFMT. These training programmes will be administered by the researcher and four trained physiotherapists with postgraduate qualification in women’s health. Two research assistants will be attached to each of the two training groups (i.e. two for PEM and two for PFMT). All trainings in both groups will be carried out in the morning. Both training programmes are structured to conform to the Consensus on Exercise Reporting Template (CERT) checklist [39, 40].

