## The Paula exercise method

The Paula exercise method will be adapted from previous studies where the method has been described in detail [27, 32]. No equipment will be needed for the exercise. The exercise will involve contracting and relaxing the eye muscles daily. The participants will first assume a comfortable sitting position on a chair (with back rest), and relax for two (2) minutes. The researcher or research assistance will teach the participant (until mastered) how to effectively contract (squeeze) the eye muscles and hold it for five (5) seconds, and then relax the muscles for three (3) seconds (this makes one exercise cycle). The exercise cycle will be repeated forty (40) times in a daily session. The same exercise procedure will be repeated daily by all the participants for twelve (12) weeks. The exercise procedure will be performed under the supervision of the researcher or any of the two research assistants during Week One of the study. Subsequently, participants will be instructed to continue with the exercise procedure at home for the remaining 11 weeks. Participants will each receive an activity log book in which to document their daily training activities (such as time training was performed and the duration of the activity) and any adverse event experienced during the training. The researcher and the research assistants will continually monitor the participants’ daily exercise performances through phone calls to ensure adherence. At four, eight and twelve weeks, each participant will be asked to visit the study centres (physiotherapy departments of either MMSH or JGH according to where the participant was recruited) to perform the exercise in group (according to the protocol specific for this group) in the presence of the researcher and/or research assistant and to re-assess the functional outcomes.

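### The protocol defines the experimental arm in two incompatible ways, as PEM plus PFMT and as PEM alone, so it is not fixed whether the trial tests adding PEM to PFMT or replacing PFMT with it.

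*Protocol article*

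**What the plan says.** The Randomization section is the only place that states in so many words what each arm receives: "PEM group where they will receive PEM plus PFMT), or the control group (where they will receive PFMT only".

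The sections on delivery describe something else:

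- Interventions: "Two research assistants will be attached to each of the two training groups (i.e. two for PEM and two for PFMT".
- The Paula exercise method: "The exercise will involve contracting and relaxing the eye muscles daily", and then "The same exercise procedure will be repeated daily by all the participants for twelve (12) weeks". The section covers teaching, one supervised week, 11 weeks at home, a log book, monitoring calls, and visits at 4, 8 and 12 weeks at which the group follows its own protocol. PFMT does not appear in it.
- Pelvic floor muscle training: a parallel, self-contained description with its own teaching (visual check, mirror), home practice, log book and group-specific visits.

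Elsewhere the arms are only named. Participants has women "randomized into the experimental (Paula Exercise Method) and control (Pelvic Floor Muscles Training) groups", and Table 1 lists "Paula exercise (experimental group) Pelvic floor muscle training (control group". The Abstract, the text of Study design and sample, and Sample size use the same pair of names.

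The objective names no comparator: "The main objective of this study is to investigate the effect of the Paula exercise method on urine leakage". The pilot is described by reference to the same arms: "The 30 subjects were randomly assigned into the two arms of the study".

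**The concern.** What the experimental arm receives determines what the trial estimates. PEM plus PFMT against PFMT alone estimates the benefit of adding PEM. PEM against PFMT estimates the effect of using one in place of the other. Neither result answers the other question.

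The Background argues for replacement. It says that PFMT needs individual professional supervision, that most fistula centres lack the staff for it, and that PEM is regarded as an alternative with comparable efficacy. If the trial is run as an add-on, every woman in the experimental arm still needs PFMT, and a favourable result would not support using PEM where PFMT cannot be taught.

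There is also a practical risk. The trial runs at two hospitals. A physiotherapist working from the Randomization section would teach both exercises to the experimental arm. One working from the Paula section would teach eye-muscle contractions only.

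**Working it through.** **Step 1: does the text fix one regimen?**

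| Section | What it implies for the experimental arm |
|---|---|
| Randomization | PEM plus PFMT (explicit) |
| Interventions | A PEM training group, staffed separately from the PFMT group |
| The Paula exercise method | A full 12-week programme of eye-muscle contractions, with no PFMT dose, teaching or log |
| Pelvic floor muscle training | Visits follow a protocol specific to the PFMT group |
| Abstract, Study design and sample, Table 1, Participants, Sample size | Arms named PEM and PFMT |
| Study objectives | No comparator named |

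The names in the fifth row prove little on their own, because the Randomization section itself calls the combined arm the PEM group. The conflict rests on the second to fourth rows. These describe how each arm is staffed, taught, followed at home and brought back for visits, and they leave PFMT out of the PEM arm. If both arms received PFMT, its protocol would not be specific to one group.

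PFMT cannot be assumed as background care either. The paragraph on discontinuation and adverse events, after the PFMT section, allows regular care to continue only where it does not involve exercise similar to the study exercises.

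**Step 2: how far apart are the two readings in prescribed training?**

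Inputs:
- PEM: 40 cycles daily, hold 5 s, relax 3 s (The Paula exercise method).
- PFMT: 40 contractions once daily, hold for a count of 7, relax for a count of 3 (Pelvic floor muscle training).
- Duration: 12 weeks for both (Table 1 and the two programme sections), so 12 × 7 = 84 days.

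Pelvic floor contractions prescribed to the experimental arm over 84 days:
- If the Paula section is complete: 0.
- If the Randomization section holds and the full PFMT dose is given: 40 × 84 = 3,360, equal to control.

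Daily training time, assuming a count lasts 1 s:
- PEM: 40 × (5 + 3) = 320 s = 5.3 min.
- PFMT: 40 × (7 + 3) = 400 s = 6.7 min.
- Experimental to control, head-to-head: 320/400 = 0.80.
- Experimental to control, add-on: (320 + 400)/400 = 1.80.

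If a count lasts 1.5 s, PFMT takes 40 × 15 = 600 s, and the ratios are 320/600 = 0.53 and (320 + 600)/600 = 1.53.

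No section states a combined dose, so the add-on figures are upper limits. All of these figures describe training dose. The document gives no basis for deriving a difference in urine leakage between the readings.

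**Step 3: does the pilot settle it?**

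No. Sample size reports median leakage of 4.53 g (PEM) and 21.61 g (PFMT) in 15 women per arm and identifies the pilot arms with those of the main study. The ambiguity therefore carries over to the effect used for planning.

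**The case against.** The strongest reply is that the Randomization section does fix the regimen. It is the only place that says what each arm receives, and its contrast between the combination and PFMT only looks deliberate. On that view the two exercise sections describe components, each under its own heading, and the real gap is narrower: the PFMT dose within the combined arm is not stated. The Paula section never says that PFMT is withheld.

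This does not hold up against the content of that section. It describes an arm rather than a component: supervision, home practice, log book and visits are all given for PEM alone, under a protocol specific to that group, and the Interventions section assigns assistants to training groups.

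Two further replies have some weight:

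- The flow diagram (Fig. 1) is not available here and may show which reading is intended. It could not remove the conflict between the written sections.
- The objective and the Discussion commit only to the effect of PEM and to whether it can be used in this condition, which an add-on trial could address. The mismatch with a replacement claim therefore rests mainly on the Background. Even so, the effect being estimated remains undefined.

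One point stands in full: which reading is intended cannot be decided from the text, so the correction should not presume it.

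**Conclusion.** The concern holds. The Randomization section conflicts with the Interventions and Paula sections about what the experimental arm receives, and nothing in the text resolves it. This is a contradiction, not a detail left to a fuller document.

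The two versions differ by up to 3,360 prescribed pelvic floor contractions per woman. They also reverse which arm trains longer: the ratio of experimental to control time is 0.53 to 0.80 if head-to-head, and up to 1.53 to 1.80 if add-on. The time ratios assume a count of 1 to 1.5 s, and the add-on figures assume full doses of both exercises. The contradiction itself depends on none of these numbers.

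It must be corrected, because until then neither the treatment to be delivered nor the meaning of the primary comparison is defined.

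**What to change.** The investigators should confirm the intended regimen and state it in the same way throughout.

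**(a) If head-to-head.** Change the Randomization section to say that the PEM group receives PEM only. Word the main objective as *the effect of PEM compared with PFMT on urine leakage*. The delivery sections, the arm names and the rationale in the Background already fit this reading.

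**(b) If add-on.** Write the PFMT programme, with its dose and teaching, into the Paula section. Rename the arm *PEM plus PFMT* in the Abstract, Study design and sample (including Table 1), Participants, Sample size and Interventions. Word the objective and conclusion as *the effect of adding PEM to PFMT*. Make no claim that PEM can replace PFMT, and acknowledge that the experimental arm also receives more training time.

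**In either case**, state under Sample size which regimen the pilot PEM arm received.

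The change itself is wording only, with no extra patients, visits or measurements. That assumes actual practice and the pilot match the confirmed regimen. If the pilot PEM arm received something different, its effect does not carry over directly and the planning assumption needs another look.

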### Primary outcome measure

The primary outcome measure is urine leakage, and it will be assessed using the 1-h clinic pad test. The 1-h clinic pad test is an effective, simple, noninvasive, valid, and reliable method recommended by the International Continence Society for quantifying the amount of urine loss that will aid in the diagnosis/quantification of urinary incontinence, as well as assessing the efficacy of certain procedures that are used in the management of incontinence [38, 39]. The procedure for the pad test will be in line with the recommendation of the International Continence Society. Each participant will be asked to empty their bladder before the test, and drink 500 ml of water. A pre-weighed Always-Ultra pad will be given to the participant to place inside her underwear. The participant is then asked to sit for 15 min. After this, the researcher will instruct the participant to cough 10 times, squat 10 times, jump up and down on the spot 10 times, and walk briskly for 10 min. After 1-h, the pad will be removed and re-weighted using the Grams weighing scale. To quantify urine leakage, the difference in the pad weight will be calculated by subtracting the original pad weight from the pad weight after 1 h. A 1 g gain in pad weight will be considered as proof of UI, and a reduction in urine leakage to < 1 g after the intervention will be considered as a cure.

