### Secondary outcome measures

The secondary outcome measures are Pelvic Floor Strength (PFS) to be measured using a perineometer; QoL to be measured using the Incontinence Quality of Life questionnaire; SF to be measured using the Female Sexual Function Index (FSFI); and Mental Health (MH) to be measured using the Hospital Anxiety and Depression rating scale (HADs). The perineometer is a highly reliable instrument used in assessing PFS with high intraclass correlation coefficient values of 0.95 and 0.88 for strength, and 0.94 and 0.83 for endurance, which indicate high within-day and between-days reliability for PFM strength and endurance respectively [42]. The PFS will be assessed according to standard protocol [42]. Each participant will be asked to lie supine with knees semi-flexed; the probe of the perineometer will be inserted into the vagina until the full extent of the compressible portion of the device is at the level of the hymen. Each participant would then be instructed to maximally contract her PFM by trying to pull her pelvic floor in and up as much as possible (as if trying to stop urine from coming out) for 2–3 s. The researcher will observe the participant to ensure that she is breathing normally. Three squeezes will be recorded at intervals of 10 s between the efforts, and the average will be recorded in cms/H_2_O as the maximum perceived strength of the PFM; the higher the reading the higher the PFS [21].

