The Female Sexual Function Index (FSFI) is a questionnaire used in the assessment of female sexual function. The questionnaire possesses good psychometric properties (high test–retest reliability for each domain r = 0.79 to 0.86, and high internal consistency (Cronbach’s values of 0.82 and above) and it is easy to administer [44]. It is a multi-dimensional questionnaire with 19 items that are self-reported for assessing SF in women. It comprises six (6) domains: desire, subjective arousal, lubrication, orgasm, satisfaction, and pain. The desire domain has 2 items with scores ranging from 1 to 5 in each item, summed up to a total score of 2 (minimum) and 10 (maximum); the arousal domain has 4 items with scores ranging from 0 to 5 in each item, summed up to a total of minimum and maximum scores of 0 and 20 respectively; the lubrication domain has 4 items with scores ranging from 0 to 5 in each item, summed up to a total of minimum and maximum scores of 0 and 20 respectively; the orgasm domain has 3 items with scores ranging from 0 to 5 in each item, summed up to a total of minimum and maximum scores of 0 and 15 respectively; the satisfaction domain has 3 items with scores ranging from 1 to 5 in each item, summed up to a minimum and maximum score of 2 and 15 respectively; and the pain domain has 3 items with scores ranging from 0 to 5 in each item, summed up to a total of minimum and maximum score of 0 and 15 respectively. An FSFI total score of less than or equal to 26.55 indicates risk for sexual dysfunction.

The Hospital Anxiety and Depression rating scale (HADs) will be used to assess mental health (MH). It is a valid and reliable questionnaire used in determining the mental status of an individual [45]. Each participant will be asked to complete the HADs after clear and detailed explanation by the researcher on how to complete the questionnaire. The HADs comprises seven questions for anxiety and seven for depression and it takes 2–5 min to complete. The anxiety and depression questions are combined in the scale; however, it is recommended that they are scored separately [46]. Both scales demonstrate good to moderate to high internal consistency; Cronbach's alpha for anxiety varied from 0.68 to 0.93 (mean 0.83) and for depression from 0.67 to 0.90 (mean.82) [45].

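### The trial is labelled outcome assessor-blinded, but the procedures as written give training and outcome testing to the same named role and do not secure the blinding

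*Protocol article*

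**What the plan says.** The protocol article makes the blinding claim twice. Study design and sample states: "The study will be a two-arm, outcome assessor-blinded RCT". Randomization adds: "Assessment of outcome will be carried out by an experienced/trained researcher, who will be blinded to the type of intervention received by participants".

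On delivery of treatment, Interventions states: "These training programmes will be administered by the researcher and four trained physiotherapists". It then splits the assistants by arm ("Two research assistants will be attached to each of the two training groups"), but makes no such split for the researcher. The sections on the Paula exercise method and on pelvic floor muscle training both give the researcher, or an assistant, first-week supervision and telephone monitoring of adherence. Both also describe visits at weeks 4, 8 and 12, at which women exercise in a group specific to their arm "in the presence of the researcher and/or research assistant and to re-assess the functional outcomes".

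On measurement, Primary outcome measure says that "the researcher will instruct the participant to cough 10 times, squat 10 times, jump up and down on the spot 10 times". For the perineometer, Secondary outcome measures says: "The researcher will observe the participant to ensure that she is breathing normally". The HADs is completed by the participant "after clear and detailed explanation by the researcher on how to complete the questionnaire". The Incontinence QoL questionnaire and the FSFI are described as self-reported, with no administrator named.

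**The concern.** Women know whether they are squeezing their eyes or their pelvic floor, so they cannot be blinded. Blinding of the assessor is therefore the only protection against knowledge of the arm that the trial claims at the point of measurement. If the person who taught a woman her exercise also tests her, that protection is lost.

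The primary outcome is exposed to this even though the pad is weighed on a scale. How much urine reaches the pad depends partly on how vigorously the woman is led to cough, squat, jump and walk. Pelvic floor strength depends on an instructed maximal effort. A systematic difference that arises in this way is built into the data, and none of the analyses listed under Data analysis could remove it afterwards.

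**Working it through.** There is no figure in the plan to reproduce and no arithmetic to run. The check compares every role given to the researcher with the two blinding statements.

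**Training roles**

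| Section | Task of the researcher | Arm |
|---|---|---|
| Interventions | Administers the programmes, with four physiotherapists | Both |
| The Paula exercise method | Teaching, week 1 supervision, phone monitoring, group visits (researcher or assistants) | PEM |
| Pelvic floor muscle training | Observing contractions, week 1 supervision, phone monitoring, group visits (researcher or assistants) | PFMT |

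**Measurement roles**

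| Outcome | Task of the researcher | Not stated |
|---|---|---|
| Urine leakage, pad test (primary) | Instructs the provocation manoeuvres | Who weighs the pad |
| Pelvic floor strength, perineometer | Observes the participant | Who inserts the probe and takes the reading |
| Mental health, HADs | Explains how to complete it | – |
| Quality of life | Not named; self-reported | Who administers it |
| Sexual function, FSFI | Not named; self-reported | Who administers it |

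The researcher is thus named in 1 of 1 primary and 2 of 4 secondary outcome procedures, and as a trainer or supervisor in both arms.

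**Do the two roles meet in one person?** The article uses the same definite term for trainer and tester, and contrasts it with the research assistants when it describes training. A site following the text would most naturally read one role. Randomization speaks instead of a researcher with the indefinite article, and never says that this person stays out of training.

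**Do training and testing meet in time?** Both intervention sections place group exercise and re-assessment of functional outcomes at the same week 4, 8 and 12 visits. Data collection procedure lists functional status as QoL, mental health, sexual function and pelvic floor strength, with leakage listed separately. Table 1 nevertheless schedules urine leakage at 4, 8 and 12 weeks. That the pad test falls at the same visits is therefore a reasonable inference, but the article does not say so outright. No section says how an assessor would be kept unaware of the arm at a visit that includes an arm-specific group session.

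**Would an assistant solve it?** No. The assistants are attached two to each arm, so an assistant who tested women from her own training group would also know the arm.

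**The case against.** The strongest reply is that the text is loose rather than contradictory. The assessor under Randomization may be someone other than the trainer, and the researcher in the outcome sections may simply mean that assessor. The article uses the term freely, for example for whoever screens women and whoever develops the proforma. This stands to the extent that a reader who infers that the blinding does not exist goes further than the document allows. It does not remove the problem. Even on the kinder reading, nothing separates the two roles, and the instructions taken literally defeat the label.

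Secondly, the pad test is scripted: fixed water intake, fixed counts of manoeuvres, a timed walk and a scale reading. This limits the room for bias but does not close it, because effort is not fixed by a count.

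Thirdly, the intervention sections say researcher and/or assistant, and they do not say who re-assesses or whether testing follows exercise. That is correct, so one cannot claim that the tester has just watched the woman exercise.

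Fourthly, a reader might infer that the researcher runs all the questionnaires and could shift every outcome. The document does not support this. Two of the questionnaires are self-reported with no administrator named, the HADs is only explained, and the perineometer test is only observed. Self-reported scores are exposed mainly to women knowing their own arm, which assessor blinding would not cure.

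Finally, a condensed article may leave procedural detail to a fuller document. That would excuse silence. Here, however, the article itself states roles that conflict with its own blinding claim.

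**Conclusion.** The point holds as an unreconciled contradiction: the outcome assessor-blinded label is not secured by the procedures, and read literally they conflict with it. The primary outcome is directly affected, because the researcher is named as leading its provocation manoeuvres. The conclusion rests on reading the researcher as the same role throughout, which is the natural reading but not the only one. It does not establish that blinding will be absent in practice.

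No size can be given. The document contains nothing from which the effect of an unblinded assessor on pad weight could be estimated. A false-positive rate computed from an assumed shift would reflect only that assumption. The matter should nevertheless be settled before outcome data are collected, because it concerns the only outcome blinding the trial claims and cannot be repaired afterwards.

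**What to change.** Reconcile Study design and sample and Randomization with the intervention and outcome sections, as follows.

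- State that the blinded assessor takes no part in training, supervision or adherence calls in either arm.
- In Primary outcome measure and Secondary outcome measures, name that assessor in place of the researcher for every pad test, perineometer test and HADs explanation after randomisation. Baseline testing, which Randomization places before allocation, needs no such restriction.
- In the two intervention sections, hold re-assessment apart from the group exercise session and away from the trainers.
- If the assessor is in fact the researcher, the researcher gives up training, which the four physiotherapists already cover.
- If none of this is feasible, delete the outcome assessor-blinded description.

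The cost is revised wording, a change of roles among existing staff and a small scheduling burden at the week 4, 8 and 12 visits, since testing and group exercise must be kept apart at both hospitals. The change leaves one exposure in place: the self-reported QoL questionnaire and FSFI will still reflect women's knowledge of their own arm, and the report should say so.
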